## Abstract

**Background:**

To reduce the global burden of tobacco use, clinical guidelines support behavioral therapy and pharmacotherapy as preferred interventions for tobacco cessation. The evidence-based behavioral interventions has consistently shown to be impactful in community settings; however, its efficacy has not been established in hospital settings. The current study aims to investigate impact of trans-theoretical-based behavioral intervention package on tobacco users suffering from non-communicable diseases attending tertiary care settings of North India.

**Methods/design:**

A two-arm randomized controlled trial (RCT) in a tertiary healthcare hospital will be performed. A total of 360 tobacco users attending NCD clinics in four departments, cardiology, neurology, pulmonary medicine, and ENT (otolaryngology), will be recruited over a period of 3 months. After ascertaining the eligibility criteria, they will be followed up to 6 months (1, 3, 6) for their tobacco use status, readiness to quit, nicotine dependence, stage of behavior change, and self-reported and biochemical validation (urine cotinine) for tobacco abstinence. Assignment of intervention including allocation concealment, sequence generation, and blinding will be done as per SPIRIT guidelines for RCT protocols.

**Discussion:**

As no strong evidence exists about the effectiveness of tobacco cessation intervention in tertiary settings, the current study will build evidence about the similar interventions in such settings.

**Trial registration:**

CTRI/2019/09/021406.

## Background

Despite laudable actions against tobacco use for over 50 years, around 1.3 billion people still use tobacco [1], causing more than 8 million deaths each year globally [2]. India alone shares the burden of 267 million tobacco consumers [3], causing 1.2 million people deaths from smoking and exposure to secondhand smoke (SHS) [4]. Furthermore, 2,30,000 deaths result from the use of smokeless tobacco each year [5]. The health consequences of severe tobacco addiction and increased tobacco consumption are tremendous [6, 7]. In particular, the rise of non-communicable diseases (NCDs), including heart disease, stroke, cancer, diabetes, and chronic lung disease, is driven primarily by tobacco use. Findings [8–10] suggests that even quitting tobacco after NCD diagnosis improves survival and quality of life.

In order to combat the problem and reduce the tobacco burden, various targets have been established globally with the initiatives such as WHO Tobacco Free Initiative (1990), WHO framework convention on tobacco control (2003) [11], WHO MPOWER policy (2008) [12], and United Nation’s Sustainable Development Goals (SDG) (2015) [13]. Similarly, the Government of India enacted the Cigarettes and Other Tobacco Products Act (COTPA) [14] in 2003 to prohibit the advertisement of and regulate trade, commerce, production, supply, and distribution of cigarettes and other tobacco products. National Tobacco Control Program (NTCP) was then launched in the year 2008 to ensure effective implementation of COTPA [15].

With the implementation of policies transforming the healthcare system, promoting evidence-based treatment for tobacco cessation is equally important to better address tobacco use and dependence. Treatments including behavioral and pharmacotherapy have shown to be effective when used alone or in combination [16, 17]. Studies have documented that the healthcare providers advice has been successful in 66% increase in quit rate than no intervention [18], and motivational interviewing was more effective than simply providing brief advice for tobacco cessation [19, 20]. For the delivery of the different behavioral interventions, various modalities like web, mobile, telephone, posters, self-help materials, videos, and other sources have gained popularity in the last few decades [21].

Hospitalization increases perceived vulnerability to the harms of tobacco use, thereby motivating the tobacco users to quit. In-person delivery of various modalities especially in hospital settings also encourages patients to quit [22]. Furthermore, after discharge, patients are likely to continue with quitting behavior with positive reinforcement through regular follow-ups [22]. Contrary, multiple challenges account for tobacco dependence treatment in hospital settings. Many clinicians do not consistently offer cessation services to patients due to lack of time due to increase workload, absence of interest, low awareness about treatment, and referral services [23] and lack of resources (drug, counselors) [24]. Secondly, physical structure of the tertiary hospital site creates barriers to implementation, such as lack of private space for intervention requiring sensitive discussion [25, 26]. Furthermore, implementation involving IT innovation also face barriers related to hospital inability to accommodate new systems and staff reporting fatigue towards new initiatives [27].

While there is some evidence on the clinical and cost-effectiveness of behavioral change interventions for quitting tobacco [28–31], there is a lack of data on the effectiveness of these interventions in the tertiary healthcare setting. To our knowledge, merely two randomized controlled trials initiated in hospital settings comparing intensive with brief intervention have been documented so far on tobacco cessation [32, 33], while no such study has been conducted in India. Moreover, earlier research investigated the self-reported change in behavior rather than biochemically verified quit rate using urinary cotinine or other parameters. Therefore, current study plans to establish the evidence for behavioral intervention when delivered among tobacco users in tertiary care hospital setting.

### Objective

To ascertain the differential effectiveness of trans-theoretical model-based behavior change communication strategies for tobacco cessation among tobacco users enrolled from tertiary healthcare settings in North India.

For the current study, we hypothesize that compared with tobacco users in the brief intervention, those in the intensive group will have higher rates of 7-day point prevalent urinary cotinine verified abstinence measured at the 6-month final visit (alternate hypothesis).

## Methods/design

### Study design and setting

The study will be a two-armed randomized controlled trial (RCT) conducted in a tertiary care institute of North India.

The tertiary care health center is at the top level of the healthcare delivery system for the public, which provides specialized consultation care, usually on referral from primary and secondary medical care institutes. They include medical colleges and advanced medical research institutes owned and controlled by the central or state government. The study institute is India's premier medical and research institute, with state-of-the-art educational, medical research, and training facilities. It has bed strength of 1960 across various departments. Four departments, viz. cardiology, pulmonary medicine, neurology, and ENT (otolaryngology), were purposively selected for the study as we expect maximum enrolment of NCD patients in these departments, which is required to assess the effectiveness of the intervention. Apart from the OPD and inpatient services, these departments provide 24 h emergency services and round-the-clock consultation services. The participants visiting four departments, viz. cardiology, neurology, pulmonary medicine, and otolaryngology for their routine check-up will be screened for their eligibility in the study until the target sample is achieved. We expect to have adequate enrolment because the selected institute is a tertiary care institute catering to almost 75,000 participants per day. Moreover, to ensure enrolment in different periods of time, pamphlets will be pasted in outpatient departments and concerned doctors shall be sensitized regarding the study.

### Study participants

While there are no generally agreed-upon definitions of heavy tobacco user, intake of 20 cigarettes per day over 10–20 years, corresponding to 10–20 pack-years, has been associated with a clinically relevant increase in morbidity and used in various studies [6, 7, 34]. Thus, considering the importance of quantifying tobacco exposure and its correlation to the risk of disease, the criteria of at-least 10 pack-years for inclusion of participants, which establishes a baseline smoking or related tobacco products exposure [35], will be used for recruiting the participants visiting tertiary healthcare setting for study. Follow-up period of 6 months was included as we expect a 20% relapse before 6 months follow-up duration [36]. The participants complying with the eligibility criteria will be informed about the study.

### Inclusion, exclusion, and dropout/withdrawal criteria

Participants will be eligible provided they (1) are above 18 years of age, (2) have a history of using tobacco for the last 1 month and at least 10 pack-year or equivalent tobacco, (3) can read and understand English, Hindi, or Punjabi, (4) have a mobile phone with text messages/WhatsApp messages accessibility, and (5) are willing to quit and provide written consent for intervention and follow-up of 6 months in the study.

Participants will be excluded if they (1) are unable to understand any of the languages as mentioned above, (2) are severely ill to participate in the study and require urgent attention for any of the medical problems, (3) are already taking treatment for tobacco cessation, and (4) are mentally ill to accord informed consent for the study.

Participants will be discontinued for the study if they (1) voluntarily withdraw the consent, (2) are not complying with the study schedule, and (3) are not in a condition to continue with the study due to migration or other reasons. The reason for withdrawal will be collected, and no more follow-up will be initiated. Participants who drop out of the study will be considered tobacco users.

Intention-to-treat will be used for data analysis, wherein all participants who are randomized to a treatment arm and receive their assigned intervention are included in the final analysis whether they complete the study or respond to follow-up surveys at study end points. This method will be used to avoid any bias that can potentially arise because of crossover and dropouts, affecting the initial random assignment to treatment groups.

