	(Motivational videos) Videos based on real life stories of patients with tobacco use history will educate and sensitize patients and care givers on harmful effects of tobacco and motivate patients to quit	3–5 min/once during first contact/researcher	Technology including mobile phones, the internet, and social media platforms, can increase access to care by extending the work of counselors and overcoming the geographical barriers. These supports can increase the likelihood of adults quitting compared with no intervention and can be a cost-effective adjunct to other treatments [39]
	(Patient information leaflet (PIL)) Patient information leaflet will be based on specific characteristics or concerns of tobacco users and include written material aiming to educate patients about the disease, ill effects of using tobacco on health, benefits of quitting and how to resist cravings and avoid relapse	Once at first contact/researcher	Providing self-help materials (primarily print-based) tailored to the individual patient (that is, beyond a brochure that simply describes the health effects of tobacco use and benefits of cessation) is effective in improving tobacco abstinence [40]
**Intensive**	(Telephone counseling) Counseling through regular telephone follow-up will provide support and encouragement to individuals who uses tobacco and want to quit or individuals who have recently quit	05–15 min/five times at < 1, 4, 6, 9, and 12 weeks in 3 months after enrolment/researcher	Telephone-based access to counseling and smoking cessation resources increases cessation rates. The majority of helplines provide access to individual counseling; the greatest amount of counselor contact, the greater the likelihood of successful cessation [41]
	(Text messages using SMS) Messages will include short text based on the current stage of behavior as per trans-theoretical model for their motivation and support regarding tobacco cessation and maintaining quit status	Bi-weekly for 3 months/researcher	Technology, including mobile phones, the internet, and social media platforms, has the power to increase access to care by extending the work of counselors and overcoming geographical barriers. These supports can increase the likelihood of adults quitting compared with no intervention and can be a cost-effective adjunct to other treatments [39]

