### Data analysis

Data analysis will be undertaken by the investigators using the SPSS statistical analysis package.

Analysis of primary outcome of 7-day point prevalence tobacco abstinence at 6 months will be based on an intention-to-treat approach. It shall be done by estimating the mean difference in percentage of quit rates between the intensive and brief intervention groups at 6 months.

Regression analysis and /or ANOVA will be used for primary and secondary outcomes. For not normally distributed data, robust standard errors, truncation, or transformation will be used. For missing data, multiple imputations will be used. The net changes in primary and secondary outcome measures will be considered by exploratory analysis. Marginal means and treatment effect with its associated 95% CI and probability values will be presented and reported. The conventional significance level of 0.05 will be used in all analyses to reject the null hypothesis of no difference between two groups.

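### Not complying with an undefined study schedule ends follow-up and counts as tobacco use, so obtainable 6-month outcomes are lost by rule

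*Protocol article*

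**What the plan says.** Three rules stand together in the protocol article, section on inclusion, exclusion and dropout/withdrawal criteria.

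- Who is discontinued: "Participants will be discontinued for the study if they (1) voluntarily withdraw the consent, (2) are not complying with the study schedule". A third ground covers migration and other reasons.
- What happens next: "The reason for withdrawal will be collected, and no more follow-up will be initiated".
- How they are scored: "Participants who drop out of the study will be considered tobacco users".

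The next paragraph of that section adopts intention-to-treat, keeps people in the analysis whether or not they complete, and gives the purpose: "This method will be used to avoid any bias that can potentially arise because of crossover and dropouts".

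The primary outcome is cotinine-validated 7-day point prevalence abstinence at 6 months, and the urine sample is taken only at that visit. The Data collection section sets assessments at 0, 1, 3 and 6 months without distinguishing the arms. Table 1 gives the intensive arm alone telephone counseling, "five times at < 1, 4, 6, 9, and 12 weeks in 3 months after enrolment", and text messages, "Bi-weekly for 3 months/researcher". The components shared by both arms are delivered once, at first contact. The article does not say which of these contacts make up the study schedule.

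**The concern.** Scoring people whose outcome cannot be obtained as tobacco users is a familiar convention in cessation trials. Here the protocol itself creates part of the missing data. Someone who misses scheduled contacts but still consents and can be reached is dropped from follow-up, and their unmeasured outcome becomes a failure. The primary endpoint then mixes two things: abstinence at 6 months and compliance with a schedule.

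What is at stake is the size of the estimated difference, its power and, if discontinuation differs by arm, its bias. No later analysis can recover a urine sample that was never requested. Multiple imputation (Data analysis section: "For missing data, multiple imputations will be used") would only replace a measurable value with a modelled one, and it does not sit with the rule that scores dropouts as users.

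**Working it through.** **Reading the rules in sequence.** Take a participant who misses earlier contacts, is abstinent at 6 months and would give a urine sample. Under the text that person is discontinued, not approached at 6 months and, reading *dropout* to include those discontinued as the section implies, counted as a user. If the assessment were attempted, the same person would count as abstinent.

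**Inputs (Sample size section).** Brief 16.8%, intensive 30.3%, difference 13.5 points, two-sided alpha 0.05, power 80%, dropout 20%, total 366, or 183 per arm.

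**Reproducing the plan's figure.** With the plan's formula:

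n = (1.960 + 0.842)² × [0.168 × 0.832 + 0.303 × 0.697] / 0.135² = 151.15, rounded up to 152 per arm.

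152 × 1.2 = 182.4, rounded up to 183 per arm, 366 in total. The stated figure is reproduced.

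**Effect of scoring discontinued participants as users.** If a share d of an arm is discontinued independently of abstinence, the observed rate is p × (1 − d). With observed rates a (brief) and b (intensive):

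power = Φ( |b − a| / √{[a(1 − a) + b(1 − b)] / 183} − 1.960 )

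The documents give only an overall 20% dropout, with no split by arm or by reason. The shares below are therefore assumptions.

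| Discontinued, brief / intensive | Observed rates | Difference (points) | Power |
|---|---|---|---|
| 0% / 0% | 16.8% vs 30.3% | 13.5 | 86.9% |
| 10% / 10% | 15.1% vs 27.3% | 12.2 | 82.0% |
| 20% / 20% | 13.4% vs 24.2% | 10.8 | 76.0% |
| 15% / 25% | 14.3% vs 22.7% | 8.4 | 55.3% |
| 25% / 15% | 12.6% vs 25.8% | 13.2 | 90.0% |

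Worked line for 20%/20%: a = 0.168 × 0.8 = 0.1344 and b = 0.303 × 0.8 = 0.2424. The standard error is √[(0.1163 + 0.1836)/183] = 0.0405. Then 0.108/0.0405 = 2.67, 2.67 − 1.96 = 0.71, and Φ(0.71) = 0.76.

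In people, 20% of 183 is 36.6 per arm. At the planning rates, about 36.6 × 0.303 = 11 quitters in the intensive arm and 36.6 × 0.168 = 6 in the brief arm would be recorded as users.

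**No true effect.** The spurious difference is p × (d_brief − d_intensive). With equal shares it is zero. With 15%/25% it is 0.168 × (−0.10) = −1.7 points to 0.303 × (−0.10) = −3.0 points, against the intensive arm. Reversing the split reverses the sign.

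**The case against.** A reader might infer that the rule falls harder on the intensive arm. The documents do not establish this. The only other use of the word *schedule* found is the caption of Table 2, which concerns data collection common to both arms. On that reading the rule is nominally equal. Text messages are received passively, no text says that a missed call triggers discontinuation, and extra contact could improve retention in the intensive arm. The inference holds only if the telephone sessions count as part of the schedule, which the article leaves open.

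A reader might also infer that the rule undoes intention-to-treat. It does not. Discontinued participants remain in their randomized arm, counted as failures, and keeping people in the analysis is a different matter from following them up. The outright departure from intention-to-treat in that section is the condition in "all participants who are randomized to a treatment arm and receive their assigned intervention are included in the final analysis", which is a separate point.

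It is also tempting to say that the unblinded researcher decides who is non-compliant. The Blinding section says that the person who delivers the intervention and assesses the outcome knows the allocation, but the article does not say who decides on discontinuation.

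The sharpest objection to the arithmetic is that part of any 20% loss would occur without this rule, and that the source of the 16.8% and 30.3% may already count dropouts as users, in which case scoring them again counts the loss twice. Both objections stand. The figures show how sensitive the comparison is and do not predict the loss that this rule alone would cause.

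None of this touches the core: the text ends outcome collection for non-compliance and scores the result as failure, in either arm.

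**Conclusion.** The point holds in this form: the protocol turns schedule non-compliance into a failure on the primary endpoint and gives up 6-month outcomes that could be measured, contrary to the section's stated aim. The loss matters even when it is balanced. A 20% share in each arm takes the difference from 13.5 to 10.8 points and power from about 87% to 76%, below the planned 80%; at 10% in each arm, power is 82%. If the shares differ, the estimate moves with them: 8.4 points and about 55% power at 15%/25%, 13.2 points and about 90% at 25%/15%. The direction of bias cannot be settled from the documents.

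These figures rest on assumed shares, on discontinuation being unrelated to abstinence, and on the planning rates being rates under complete follow-up.

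**What to change.** - Remove schedule non-compliance as a reason to end outcome follow-up.
- Record missed intervention contacts as adherence data, separately from withdrawal of consent.
- Attempt the 6-month self-report and urine cotinine in everyone who has not withdrawn consent to follow-up.
- Count as dropouts only those whose 6-month outcome is not obtained.
- State which contacts make up the study schedule, and reconcile the scoring of dropouts as users with the multiple imputation planned in the Data analysis section.

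The cost is a change of wording and some extra contact attempts at 6 months, within the follow-up already planned. The intervention in either arm does not change.

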#### Implementation

Prior to opening envelopes, the eligibility of participants shall be assessed by the researcher. Eligible participants will then be informed about the trial and asked for their participation. After that, the interested participants will then be enrolled in the intervention arms and provided with the assigned intervention by the study researcher.

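### The set labelled intention-to-treat also requires receipt of the assigned intervention, so as written it is a modified ITT set that could favour the intensive arm

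*Protocol article*

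**What the plan says.** The only definition of the analysis set is in the Protocol article, under Inclusion, exclusion, and dropout/withdrawal criteria. It says that "all participants who are randomized to a treatment arm and receive their assigned intervention are included in the final analysis", and the sentence goes on: "whether they complete the study or respond to follow-up surveys at study end points". The purpose follows: "This method will be used to avoid any bias that can potentially arise because of crossover and dropouts". The preceding paragraph adds: "Participants who drop out of the study will be considered tobacco users".

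The Data analysis section relies on this without redefining it: "Analysis of primary outcome of 7-day point prevalence tobacco abstinence at 6 months will be based on an intention-to-treat approach".

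What there is to receive differs by arm. In Table 1 (Intervention/treatment arm), counselling, video and leaflet are given once, at first contact, in both arms. The intensive arm alone adds telephone counselling, "five times at < 1, 4, 6, 9, and 12 weeks in 3 months after enrolment", and text messages for three months. Under Blinding, the trial is open-label, and the researcher who delivers the intervention also assesses the outcome.

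**The concern.** The definition joins two conditions. Randomisation is fixed at baseline. Receipt is met or failed afterwards and can depend on the arm and on the participant's motivation. A set with such a condition is not intention-to-treat, whatever its label.

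It also works against its own stated purpose. The brief package is contained in the intensive one, so someone assigned to intensive who ends up with only the brief components has not received the assigned intervention. On a strict reading that person leaves the analysis, although crossover is one of the two things the method is meant to guard against.

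At stake is the primary comparison. If receipt includes the calls and texts, non-receipt is much easier in the intensive arm. People who do not take up calls are plausibly less likely to quit, so removing them would raise the analysed quit rate in the arm that the hypothesis favours. Because receipt is undefined, an unblinded researcher would also have to judge who received the intervention.

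**Working it through.** **The wording, part by part**

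- Entry to the set: randomised, and received the assigned intervention. The second part is a post-randomisation condition.
- Once in the set: kept whether or not the participant completes the study or answers follow-up surveys.
- Dropouts: counted as tobacco users.
- Nothing regroups participants by the treatment they actually had. The assigned arm is retained.

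This describes a modified intention-to-treat set. It comes close to per-protocol if receipt means every component, and close to full intention-to-treat if receipt means only the first-contact session.

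**The plan's sample size, reproduced**

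The Sample size section gives 16.8% and 30.3%, two-sided α of 0.05 and 80% power.

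n = 7.849 × (0.168 × 0.832 + 0.303 × 0.697) / 0.135² = 151.1, so 152 per arm. Then 152 × 1.2 = 182.4, so 183 per arm and 366 in total, as stated. The 183 per arm is used below. The point about the analysis set does not depend on it.

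**Size of the possible bias**

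From the document: 183 per arm, and 16.8% as the common abstinence rate p. Assumed, and not in the document: no true effect, exclusions from the intensive arm only, a fraction e excluded, and abstinence r among those excluded.

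- Analysed intensive rate = (p − e·r)/(1 − e)
- Bias d = e(p − r)/(1 − e)
- Rejection probability = Φ[(d − 1.96·SE₀)/SE₁] + Φ[(−d − 1.96·SE₀)/SE₁], where SE₀ is the pooled and SE₁ the unpooled standard error, with 183 against 183(1 − e)

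Worked case, e = 0.20 and r = 0.084 (half of 16.8%): (0.168 − 0.0168)/0.80 = 0.189, so d = +2.1 points. With 183 against 146.4, SE₀ = 0.0424 and SE₁ = 0.0426, and the rejection probability is 0.080.

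| Excluded from intensive arm | r = 8.4%: bias, type I error | r = 0%: bias, type I error |
|---|---|---|
| 0% | 0, 5.0% | 0, 5.0% |
| 5% | +0.4 points, 5.2% | +0.9 points, 5.6% |
| 10% | +0.9 points, 5.6% | +1.9 points, 7.5% |
| 20% | +2.1 points, 8.0% | +4.2 points, 16.5% |

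Taking r as exactly 8% gives +2.2 points at 20% excluded, with type I error still about 8%. If those excluded quit at the same 16.8% as everyone else, the bias is zero at any e. The planned difference is 13.5 points.

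**The case against.** The strongest reply is that the receipt phrase should be read with the rest of its sentence. An intensive-arm participant who stops answering calls is naturally a non-completer, so is kept, and the dropout rule counts dropouts as tobacco users. Such people would stay in the denominator as failures, which does not inflate the intensive quit rate. Delivery also starts straight after allocation: "the interested participants will then be enrolled in the intervention arms and provided with the assigned intervention by the study researcher". If receipt means that first contact, which has the same content in both arms, exclusions should be few and similar. Texts are sent by the researcher, and a phone that can receive messages is an eligibility condition, so receiving them takes little effort. The exclusion fractions above are not in the protocol either.

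Much of this stands. It shows that the bias may be nil and that no particular size can be claimed. It does not remove the defect, because the protective clauses apply only to people already in the set, and the protocol nowhere says that receipt means the first contact. Even on the mildest reading, a randomised participant who did not get that contact is left out.

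A reader might infer that this is an as-treated analysis. It is not, because nobody is moved to the arm of the treatment actually received. A reader might also infer that the randomised comparison is necessarily broken. The document does not support that, because it depends on how receipt is applied and on who would be excluded.

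**Conclusion.** The point holds in a limited form. The written definition is a modified intention-to-treat set with an undefined receipt condition. It contradicts its own label and its stated aim regarding crossover, and the Data analysis section carries it into the primary outcome unchanged. This is a definition the article states wrongly, rather than detail left to a statistical analysis plan.

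The consequence is a risk, not a demonstrated bias. It is zero if every randomised participant counts as having received the intervention. It is about 1 to 2 points, with type I error of about 5.6% to 8%, if 10% to 20% of the intensive arm alone were excluded and quit at about half the overall rate. It would be larger if none of those excluded quit. All of these figures rest on assumed exclusion patterns. Under those patterns the error favours the trial's hypothesis, which is reason enough to correct the sentence before analysis.

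**What to change.** Replace the definition with wording such as: all randomised participants are analysed in the arm to which they were randomised, whether or not they received any or all of the assigned intervention, and whether or not they completed follow-up. Have the Data analysis section refer to that definition for the primary outcome.

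Report receipt of calls and messages descriptively. If an analysis restricted to those who received the intervention is wanted, define receipt for each arm in advance and label that analysis supplementary.

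The cost is one sentence in the protocol or analysis plan. It needs no new data and no change to the sample size, since the denominator is simply everyone randomised (183 per arm as planned).
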